## Abstract

**Introduction:**

The traumatic death of a loved one, such as death due to a traffic accident, can precipitate persistent complex bereavement disorder (PCBD) and comorbid post-traumatic stress disorder (PTSD) and depression. Waitlist-controlled trials have shown that grief-specific cognitive–behavioural therapy (CBT) is an effective treatment for such mental health problems. This is the first study that will examine the effectiveness of online CBT (vs waitlist controls) in a sample exclusively comprised of people bereaved by a traumatic death. Our primary hypothesis is that people allocated to the online CBT condition will show larger reductions in PCBD, PTSD and depression symptom levels at post-treatment than people allocated to a waitlist. We further expect that reductions in symptom levels during treatment are associated with reductions of negative cognitions and avoidance behaviours and the experience of fewer accident-related stressors. Moreover, the effect of the quality of the therapeutic alliance on treatment effects and drop-out rates will be explored.

**Methods and analysis:**

A two-arm (online CBT vs waiting list) open-label parallel randomised controlled trial will be conducted. Participants will complete questionnaires at pretreatment and 12 and 20 weeks after study enrolment. Eligible for participation are Dutch adults who lost a loved one at least 1 year earlier due to a traffic accident and report clinically relevant levels of PCBD, PTSD and/or depression. Multilevel modelling will be used.

**Ethics and dissemination:**

Ethics approval has been received by the Medical Ethics Review Board of the University Medical Center Groningen (METc UMCG: M20.252121). This study will provide new insights in the effectiveness of online CBT for traumatically bereaved people. If the treatment is demonstrated to be effective, it will be made publicly accessible. Findings will be disseminated among lay people (eg, through newsletters and media performances), our collaborators (eg, through presentations at support organisations), and clinicians and researchers (eg, through conference presentations and scientific journal articles).

**Trial registration number:**

NL7497.

Strengths and limitations of this studyThis study is the first to examine the effectiveness of online cognitive–behavioural therapy (CBT) (vs waitlist controls) in reducing psychopathology after traumatic loss in a randomised controlled trial.This study is one of the first to examine potential correlates of change in symptom levels following online treatment after traumatic loss.We are not able to formally test mediators or moderators of treatment effects.We are not able to examine if online CBT has equal effects as face-to-face CBT.We are not able to establish formal diagnoses, as we use self-report questionnaires, instead of diagnostic interviews, to assess symptom levels.

## Introduction

Worldwide, traffic accidents represent the leading cause of unnatural deaths.^1^ A total of 10%–20% of bereaved people who experience natural deaths (eg, illness) develop severe and persistent grief-related distress, including persistent complex bereavement disorder (PCBD), post-traumatic stress disorder (PTSD) and depression.^2 3^ Notably, PCBD has been introduced as other specified trauma-related and stressor-related disorder, in the latest version of the Diagnostic and Statistical manual of Mental Diseases (DSM-5).^4^ PCBD can be diagnosed if, after the death of a significant other at least 12 months earlier, a person experiences persistent yearning for the deceased and symptoms of reactive distress (eg, emotional numbness) and social/identity disruption (eg, feeling alone) causing impairment in daily life. While some PCBD symptoms overlap with PTSD (eg, anger) and depression symptoms (eg, diminished interest in activities), several studies have shown that these three syndromes are distinct.^5–7^ Unexpected/violent losses of a significant other, also referred to as a traumatic losses, including deaths caused by traffic accidents, increase risks for the development of PCBD, PTSD and depression.^8 9^

## Heightened risk for developing psychopathology after deaths due to traffic accident

Specific circumstances of losses caused by accidents may account for the elevated risk of grief-related distress. For instance, experiencing multiple losses simultaneously, being a witness to the accident, and juridical and financial consequences are proposed to exacerbate grief-related distress.^10^ Furthermore, negative cognitions and avoidance behaviours may mediate the influence of sudden/violent loss on grief, PTSD and depression levels.^11^ According to a cognitive–behavioural model, three interacting malleable processes underlie disturbed grief reactions: (1) negative cognitions, (2) avoidance behaviour and (3) difficulties integrating the loss into the autobiographical knowledge base.^12^

Experiencing a loss due to a traffic accident may violate basic assumptions about the world being a safe place.^13^ This may fuel negative cognitions (eg, ‘I’m less worthy, since s/he died’ and ‘The death of him/her has taught me that the world is unjust') that may exacerbate and maintain acute grief responses.^14^ Avoidance behaviours include depressive avoidance and anxious avoidance strategies. Depressive avoidance refers to withdrawal from social and occupational activities that were perceived as fulfilling before the death, out of the conviction that these activities are no longer meaningful. Anxious avoidance strategies serve to prevent confrontation with the reality of the death, out of fear that confrontation is too painful.^12^ One potential way to avoid confrontation with the reality of the loss is to focus on angry thoughts and feelings (eg, ‘I was angry at the police, courts, or administration, because they did not do their work well enough’).^15^ This seems to be a frequently used avoidant coping strategy in bereaved people after traffic accidents and is strongly related to PTSD.^16^ Difficulty with integration of the loss into the autobiographical knowledge base refers to the difficulties connecting factual knowledge that the loss is irreversible with existing information about the self and the relationship with the lost person, stored in autobiographical memory. Memories related to the loss may lack context in terms of time and place, causing the loss to be experienced as unreal.^17^ It has been argued that this ‘sense of unrealness’ may trigger intrusive memories and increase feelings of numbness or shock once the bereaved person is confronted with reminders of the loss.^17 18^ The extent to which a person believes that one is capable of managing stressor-related thoughts, emotions and behaviours, also referred to as self-efficacy (eg, ‘I can usually handle whatever comes my way’), has also been determined as an important factor facilitating coping with traumatic stressors.^19^ Decreased self-efficacy, negative cognitions and insufficient integration of the loss may contribute to increased sensitivity to loss reminders or secondary stressors following traumatic loss.^20^

## CBT for grief-related distress

Grief-specific CBT has been demonstrated to be the most effective treatment for bereaved people with elevated grief levels.^21–24^ CBT targets the abovementioned cognitive-behavioural variables with cognitive restructuring, loss-related exposure and behavioural activation. Notably, research on putative mechanisms of change of grief-specific CBT is sparse^23^ (but see refs 25 26). Examining the effectiveness of grief-specific CBT and its potential mechanisms of change in traumatically bereaved people with traumatic grief is clinically relevant because it would enable tailoring of interventions to the specific needs of this group, which could improve treatment outcomes.^27^

While the majority of trials assess the efficacy of face-to-face CBT,^24^ so far, to the best of our knowledge, three online CBT-based interventions have been developed for distressed bereaved people.^28–30^ These prior studies provided preliminary data on the potential effectiveness of online grief-specific CBT, but had some limitations. For instance, treatment was solely provided to people who experienced perinatal loss^29^ or included relatively small samples.^28^ Comparability between these three studies is also limited, because interventions differed in treatment content; different elements of CBT were offered, for instance, behavioural activation, exposure^28^ or writing assignments.^29 30^ Offering CBT via the internet has some potential advantages. It may lower the threshold for seeking treatment, because it can be delivered independent of geographical location. Furthermore, asynchronous communication may be used, allowing the client and therapist can contact each other at any preferred time.^31^ This may counter barriers to mental health service use, such as difficulties with finding help, transportation concerns or difficulties scheduling treatment sessions.^32^ In addition, online CBT could reduce treatment costs, improving accessibility and dissemination of care for people in need of support.^33^ Moreover, during times of a crisis, such as the COVID-19 pandemic, it seems more relevant than ever to further examine the effectiveness of online CBT for distressed bereaved people, as it will allow them to retain access to evidence-based care.^34^

A potential downside to online CBT is the high dropout rate found in earlier studies.^33 35^ It has been argued that a strong therapeutic alliance might support adherence to online treatment and mediates treatment effects.^36^ Therapeutic alliance is defined as a positive emotional bond between client and therapist, whereby both parties agree on the tasks and goals of the treatment.^37^ The client–therapist relationship might also explain why online treatments are more effective with therapist guidance than without.^31^ Concerns have been raised that developing a therapeutic relationship might be more difficult when non-verbal communication is absent.^38^ However, studies in non-bereaved samples indicate that developing a strong therapeutic alliance is possible during online treatment^33^ and that therapeutic alliance is often related to online treatment outcomes,^39^ but not always.^33^ More research is needed to further examine the interrelations of the quality of client–therapist relationship, drop-out and treatment outcomes in online CBT.

## Study objectives

Our first aim is to examine the effectiveness of online CBT (vs a waiting list control condition) in reducing symptom levels of PCBD, PTSD, and depression in people bereaved by a traffic accident. We expect that participants assigned to the online CBT condition will show larger reductions in symptom levels of PCBD, PTSD and depression compared with waitlist controls at post-treatment assessments (hypothesis 1).

Our second aim is to explore correlates of change. Based on prior research and theories,^12 16 19^ we expect that reductions in negative cognitions, avoidance behaviours, state anger, a sense of unrealness and improvement in self-efficacy are related to reductions in PCBD, PTSD and depression levels in online CBT (hypothesis 2a). Additionally, we aim to explore whether background characteristics (ie, gender, age and educational level, kinship to the deceased and time since loss) and accident-related stressors (ie, single vs multiple loss, witnessing the accident and status of legal trial) are related to treatment effects (hypothesis 2b). We have no specific expectations regarding these associations because prior treatment studies in bereaved people showed inconsistent results.^24 25 40^ However, based on clinical experience, we expect that accident-related stressors are associated with treatment effects, such that multiple loss, witnessing the accident and ongoing legal trial negatively impact treatment effects.

Our third aim is to explore the associations between quality of the therapeutic alliance and drop-out rates and treatment outcomes. We expect that a stronger therapeutic alliance is related to lower drop-out rates and better treatment outcomes.

## Methods and analysis

### Design

A two-arm (online CBT vs waiting list) multicentre open label parallel randomised controlled trial (RCT) will be conducted. Randomisation will take place after the participant is screened for eligibility-based inclusion criteria (described below). A random number generator (www.random.org) will be used by a blinded independent researcher, to perform the blocking randomisation procedure. An allocation ratio of 1:1 will be applied.

Participants allocated to the online CBT condition receive treatment within 1 week after allocation. All participants will be asked to fill in questionnaires (described below) at baseline (T1), 12 weeks postallocation (T2 for the intervention condition and T1a for waitlist controls) and 20 weeks postallocation (T3 for the intervention condition and T1b for waitlist controls). For participants in the waiting list control group, at the end of the 20-week waiting period after which they will receive online CBT, they will be asked to fill in T2 and T3 12 and 20 weeks after starting treatment, respectively (see figure 1). A link to online questionnaires will be sent to the participants by a non-blinded member of the research team at each time point. A waitlist control group (instead of a no treatment control group) is chosen to increase the likelihood of continued study participation by guaranteeing that all participants receive treatment. Furthermore, the inclusion of a waiting list control group allows a treatment versus no treatment comparison that will provide knowledge about the effects of treatment relative to natural recovery from loss.

**Figure 1 F1:**
[figure not shown]
Design of RCT. CBT, cognitive–behavioural therapy; RCT, randomised controlled trial.

In line with prior treatment studies from our research group,^40 41^ the online treatment is guided by governmentally licensed psychologists, connected with a Dutch informal ‘traumatic loss network’ of therapists specialised in treating emotional distress following traumatic loss. In total six therapists (including authors PB and [name] who are registered clinical psychologists) will guide the participants online; participants will receive feedback from the same therapist each time. The therapists will receive a training, provided by LL, PB and [name], on the use of the treatment protocol of this intervention study. In preparation for the training, therapists read all treatment materials and a selection of grief treatment literature. Instructions about the use of the online treatment interface will be given by its developers. During a 5-hour face-to-face group meeting the rationale of the online treatment will be explained and research procedures will be discussed. In a 2-hour online video meeting outstanding questions regarding the treatment and the research project will be answered. Supervision (by telephone or email) by PB and [name] is possible on request, for instance, when therapists encounter difficulties in treatment. Therapists will be contacted by a member of the research team by phone or email biweekly to monitor treatment progress and protocol adherence. Treatment costs will be reimbursed.

### Participants

This RCT is part of a larger ongoing research project (the ‘TrafVic-project’) examining the psychological impact of, and care after, the death of a loved one due to a traffic accident. We expect to recruit the majority of the participants via a survey that started in December 2018 and included the following question: ‘In this study we would like to offer psychological help to persons who experience emotional problems. May we approach you with more information about this offer, if your answers to this questionnaire show that you experience emotional problems?’ Those who answered ‘yes’ will be sent a letter with information about the intervention, the treatment study and an informed consent form (see online supplementary file). A Dutch website (www.rouwnaverkeersongeval.nl) has been developed so that potential participants can read information about the research and treatment. People who are interested can also sign up for the study via this website. Recruitment for this RCT had not started at the time of submission of this manuscript.

10.1136/bmjopen-2019-035050.supp1Supplementary data

To be eligible for study participation, the person must (1) be a family member, spouse or friend of a person who died due to a traffic accident at least 1 year earlier, (2) be ≥18 years of age and (3) meet DSM-5 criteria for PCBD and/or PTSD and/or experience clinically relevant depression, based on questionnaire scores (see below for more details). People are excluded when they do not master the Dutch language or have no internet access.

### Sample size

To test our primary hypothesis (hypothesis 1), a test for each outcome separately (PCBD, PTSD and depression) will be conducted to assess the effects of online CBT versus waitlist controls. To find a difference between two groups (online CBT vs waitlist controls) of at least a medium effect size (f=0.25; based on prior research^22 28 40^) with a power of 80%, an α of 0.017 (corrected for multiple testing, that is, 0.05/3, as there are three primary outcome measures (PCBD, PTSD and depression), and a strong association (r=0.50) between the preassessment and postassessment, a sample size of 23 per condition is sufficient. Taking into account an average dropout rate of 19%,^22^ a total sample size of 55 (46+9) is required to test hypothesis 1.

Because our data are nested (repeated measures) (level 1) within individuals (level 2), and possibly within families sharing the same household (level 3), multi-evel modelling will be performed to test hypothesis 1. Conducting a power analysis within a multilevel framework is not feasible for various reasons.^42^ Our power analysis is therefore based on a repeated measures analysis of variance.

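### The sample size is described as powered for a medium difference between two groups, but 23 per condition gives 80% power only for a between-arm difference in change of about 1.0 SD

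*Protocol article*

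**What the plan says.** The Sample size section of the protocol article sets out the target as follows.

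- Contrast: "To find a difference between two groups (online CBT vs waitlist controls".
- Effect: "of at least a medium effect size (f=0.25; based on prior research".
- Error rates: "with a power of 80%, an α of 0.017 (corrected for multiple testing", obtained as 0.05/3 for three primary outcomes.
- Correlation: "a strong association (r=0.50) between the preassessment and postassessment".
- Result: "a sample size of 23 per condition is sufficient", raised to 55 in total for dropout.
- Method: "Our power analysis is therefore based on a repeated measures analysis of variance".

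The section does not say whether f belongs to a between-group effect or to the interaction. It gives no equivalent in SD units or scale points. The Statistical analyses section tests hypothesis 1 with a model containing condition, time and their interaction, and its stated aim is to compare reductions in symptoms between the arms.

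**The concern.** Cohen's f does not carry the same meaning from one ANOVA effect to another. For a plain comparison of two groups, f is half the standardised mean difference, so f=0.25 is 0.5 SD, the usual medium difference. For the interaction in a two-group, two-occasion design, the same f corresponds to a difference in change twice that size. The section describes the first and appears to have calculated the second.

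The stated power is what a reader uses to judge a non-significant result. Each of the three primary outcomes is tested at 0.017. Someone who takes the sentence at face value would expect a true 0.5 SD benefit on any one of them to be found four times in five.

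**Working it through.** **Inputs (Sample size section):** f = 0.25; alpha = 0.017; r = 0.50; 23 per condition, N = 46. Two occasions (m = 2) are inferred from the single pre-post correlation. The F test with 1 numerator df corresponds to a two-sided test.

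**Step 1. Reproduce the plan's figure.** For the time-by-condition interaction:

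λ = N·f²·m/(1−r) = 46 × 0.0625 × 2/0.5 = 11.5, on F(1, 44). Power = 81.4%.

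N = 44 gives λ = 11.0 and 79.3%, so 46 is the smallest even total that reaches 80%. Other versions do not give 46:

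| Test | Total N for 80% power |
|---|---|
| Interaction, 2 occasions, alpha 0.017 | 46 |
| Interaction, 3 occasions, alpha 0.017 | 36 |
| Interaction, 2 occasions, alpha 0.05 | 34 |
| Between-group effect, 2 occasions, alpha 0.017 | 128 |
| Between-group effect, 3 occasions, alpha 0.017 | 116 |

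**Step 2. Convert f to a difference in change.** In a 2×2 interaction each of the four cell means deviates by f·SD, so the difference in change between arms is 4·f·SD = 4 × 0.25 = 1.0 SD. As a check, the SD of change is SD·√(2(1−r)) = SD·√1.0 = 1.0 SD. A two-group test on change scores then has λ = (N/4)·d²/[2(1−r)] = 11.5·d². Setting this equal to 11.5 gives d = 1.0.

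**Step 3. Take the wording literally.** For a between-group effect:

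λ = N·f²·m/[1+(m−1)r] = 46 × 0.0625 × 2/1.5 = 3.83, on F(1, 44). Power = 31%. Reaching 80% needs N = 128.

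**Step 4. What 23 completers per arm can detect.** Here λ = (23/2)·d²/v, where v is the variance factor in units of SD². The same F(1, 44) is used throughout, ignoring the one df spent on a baseline covariate. Rows 3 and 4 assume r = 0.5 between all three occasions, which the protocol does not state.

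| Analysis | v | Power, 0.5 SD | Power, 0.8 SD | Difference with 80% power |
|---|---|---|---|---|
| Change, one post assessment | 2(1−r) = 1.00 | 23% | 59% | 0.98 SD |
| Baseline-adjusted, one post assessment | 1−r² = 0.75 | 31% | 74% | 0.85 SD |
| Change, mean of two post assessments | (1+r)/2 + 1 − 2r = 0.75 | 31% | 74% | 0.85 SD |
| Baseline-adjusted, mean of two post assessments | (1+r)/2 − r² = 0.50 | 47% | 91% | 0.70 SD |

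On one post assessment, 80% power for 0.5 SD would need 85 per arm (change) or 64 per arm (baseline-adjusted).

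**Step 5. Sensitivity.** With 27 per arm, roughly the full enrolment with no dropout, power for 0.5 SD on one post assessment is 27% (change) or 37% (baseline-adjusted). At an assumed r = 0.8 with 23 per arm it would be 58% or 64%, but the protocol fixes r at 0.50.

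**The case against.** The strongest reply is that nothing has been miscalculated. The section names a repeated-measures ANOVA, f=0.25 carries the conventional medium label for ANOVA, the interaction is the term that tests hypothesis 1, and the inputs give 46 for that term. The protocol never mentions d=0.5 or half an SD. All of this stands, and a reader who infers an arithmetic error would be wrong. It does not rescue the description: the section attaches f to a difference between two groups and never says that it belongs to the interaction.

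A second reply is that the effect rests on cited prior research. Those studies are not at hand, so whether a difference near 1.0 SD against a waiting list is realistic cannot be judged. A reader might infer that the trial is too small for the effect its sources support; the documents do not show that.

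A third reply is that the planned analysis is richer than two occasions with completers only. There are assessments at baseline, 12 and 20 weeks, and all entrants are to be included in a multilevel model. This is fair, and it is why the 23–31% range should not be presented as the power of the planned analysis. Averaging both post-allocation assessments raises it to about 31–47%, still well short of 80%.

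Two further inferences should be resisted. The statement that a multilevel power analysis is not feasible cannot be blamed for hiding the problem: such a calculation also needs an effect on a chosen scale and could carry the same ambiguity. Nor does the protocol claim that a non-significant result would rule out a medium benefit. That risk lies with readers of the power statement.

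**Conclusion.** The point holds as a mis-described effect size. The 23 per condition is right for a two-occasion interaction with f=0.25, which is a between-arm difference in change of about 1.0 SD (0.98 SD at exactly 80% power, or about 0.85 SD baseline-adjusted). It does not give 80% power for a 0.5 SD difference between groups, which is how the sentence is most naturally read. With 23 completers per arm, a true 0.5 SD benefit on a given outcome would be missed in about 69–77% of trials on one post assessment, and in about 53–69% if both are averaged.

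These figures rest on the protocol's alpha of 0.017 and r=0.50. Those for the averaged analysis also assume r=0.5 between all occasions. The 1.0 SD is in units of the cross-sectional SD, which equals the SD of change only because r=0.50.

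**What to change.** Keep the enrolment target and reword the Sample size section.

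1. State that f=0.25 refers to the time-by-condition interaction in a two-group, two-occasion repeated-measures ANOVA.
2. Replace the phrase about a difference between two groups of at least medium size with the detectable difference. For example: with 23 completers per arm, alpha 0.017 and r=0.50, a two-occasion analysis has about 80% power for a between-arm difference in change of about 1.0 SD, or about 0.85 SD with baseline adjustment.
3. Add that power for a 0.5 SD difference is well below 80% (23–31% on one post assessment; about 31–47% if both post-allocation assessments are averaged, assuming r=0.5 between all occasions), so a null result cannot exclude a benefit of that size.
4. State what difference, in SD or scale points, the cited prior research supports.

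Simulating the planned multilevel model would be a useful optional check. The cost is a few sentences and a less favourable stated detectable effect. No extra participants are needed, and alpha, outcomes and analysis do not change. The article reports that recruitment had not begun at submission, so the wording could be settled before any trial data exist.

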### Statistical analyses

To examine the differences in reductions of symptom levels of PCBD, PTSD and depression from pretreatment to post-treatment/waiting period between the conditions (online CBT vs waitlist), three independent multilevel models will be built (hypothesis 1). Symptom levels of PCBD, PTSD, and depression will consecutively be included as dependent variables and condition (online CBT vs waitlist controls), time and time × condition (interaction term) as predictor variables, taking into account that repeated observations (level 1) are nested within individuals (level 2), and within households (level 3; if applicable). Additionally, relevant background, loss-related variables and use of cointerventions (yes/no) during participation in our study will be included in the analysis as covariates. Deviance tests will be used to examine whether inclusion of these covariates improves model fit.^57^ Data of all participants entering the study will be included in all analyses (ie, intention-to-treat analysis). Furthermore, percentages of people meeting diagnostic criteria for PCBD, PTSD and clinically relevant depression will be calculated for each measurement occasion and percentages of people reporting reliable change scores for each outcome measure, using a formula from Jacobson and Truax,^58^
^p 14^ will be reported.

To examine to what extent symptom improvement after treatment is related to improvement in possible correlates of change, residual gain scores will be calculated for all outcome measures (ie, PCBD, PTSD and depression) and possible correlates of change (ie, negative cognitions, avoidance behaviours, state anger, a sense of unrealness and self-efficacy). Following previous research^59^, residual gain scores will be calculated by subtracting the standardised combined pretreatment scores of both conditions (T1 data from immediate treatment condition and T1b data from waitlist condition) multiplied by the correlation coefficient between standardised combined pretreatment scores and standardised post-treatment (or follow-up) scores from standardised post-treatment (or follow-up) scores. To test hypothesis 2a, multiple regression analyses will be conducted to examine the associations between residual gain scores of PCBD, PTSD or depression and residual gain scores of negative cognitions, avoidance behaviours, state anger, a sense of unrealness and self-efficacy.

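### The fixed 0.05/3 threshold for the three hypothesis 1 tests is valid but stricter than needed; Holm's procedure keeps the 5% familywise error and raises power at no cost in enrolment

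*Protocol article*

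**What the plan says.** Under Study objectives, hypothesis 1 expects that "participants assigned to the online CBT condition will show larger reductions in symptom levels of PCBD, PTSD and depression compared with waitlist controls". Under Sample size the article explains how this is tested: "a test for each outcome separately (PCBD, PTSD and depression) will be conducted". The design inputs are "at least a medium effect size (f=0.25"), 80% power, a pre-post correlation of 0.50 and "an α of 0.017 (corrected for multiple testing, that is, 0.05/3, as there are three primary outcome measures"). They lead to 23 per condition. After an allowance for 19% dropout, the section concludes that "a total sample size of 55 (46+9) is required to test hypothesis 1". Under Statistical analyses, "three independent multilevel models will be built (hypothesis 1"), one per outcome.

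The article does not say whether hypothesis 1 is confirmed by one, some or all of the three results. It gives no correlation between the outcomes. The value 0.017 appears only in the Sample size section.

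**The concern.** Dividing alpha by three and holding every test at that level is the simplest way to control the chance of any false claim across three outcomes. It is also the least efficient of the standard ways. Once one outcome has been rejected at 0.05/3, at most two true nulls can remain, so going on to test the others at 0.05/3 spends less error than is allowed. With only 23 completers per arm, the unused error matters. If the treatment works on all three symptom domains, an outcome can miss 0.017 although a procedure with the same error guarantee would have counted it. The trial could then be read as showing benefit for some symptoms only. The article makes public release of the treatment depend on its being shown effective, so a mixed result would be awkward. Recruitment had not started at submission, so the rule could still be prespecified.

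**Working it through.** **Inputs from the Sample size section.** f = 0.25, r = 0.50, alpha = 0.05/3, 23 per arm (N = 46), power based on a repeated-measures ANOVA. With two time points (m = 2), the relevant test is the group-by-time interaction.

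**Inputs assumed here.** The correlation between the three outcomes' change scores is not given; it is varied over 0, 0.3, 0.5 and 0.7, with 0.9 as an extreme. The effect is taken as f = 0.25 on each outcome. Tests are two-sided, and only rejections in favour of treatment are counted.

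**Step 1: reproduce the plan's figure.** The noncentrality is

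λ = f² × N × m / (1 − r) = 0.0625 × 46 × 2 / 0.50 = 11.5.

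Power of F(1, 44) with λ = 11.5 is 81.2% at 0.05/3 and 81.4% at 0.017. N = 46 is the size at which this test reaches 80%, so the plan's 23 per condition is confirmed as a per-outcome calculation. At 0.05 the power is 91.2%.

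**Step 2: express the effect as a difference in change.** √11.5 = 3.39, and for a two-sample t test the noncentrality is δ × √(23/2) = 3.39 δ. So δ = 1.0 SD of change.

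**Step 3: compare procedures when all three outcomes benefit.** Simulation of three equicorrelated normal change scores, 23 per arm, δ = 1.0 on each, 200,000 trials per setting. Holm compares the smallest p with 0.0167, the next with 0.025 and the largest with 0.05, stopping at the first failure.

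| Correlation (assumed) | 0 | 0.3 | 0.5 | 0.7 | 0.9 |
|---|---|---|---|---|---|
| Per-outcome power, fixed 0.05/3 | 81% | 81% | 81% | 81% | 81% |
| Per-outcome power, Holm | 90% | 89% | 88% | 87% | 86% |
| All three significant, fixed 0.05/3 | 54% | 59% | 63% | 67% | 73% |
| All three significant, Holm | 75% | 77% | 79% | 81% | 84% |
| All three significant, each at 0.05 | 76% | 78% | 80% | 83% | 86% |

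Hand check at correlation 0: 0.812³ = 0.535 for the fixed threshold, and 0.912³ = 0.759 for each test at 0.05. Both agree with the table.

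**Step 4: error control.** With two effective outcomes and one null outcome, false rejection of the null outcome in the favourable direction under Holm is 0.021 to 0.025. The two-sided error therefore stays at or below 0.05.

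**Step 5: when fewer outcomes benefit.** In the same simulation with 100,000 trials (correlations 0, 0.5 and 0.7), an effect on two outcomes only gives each of them about 84% under Holm. An effect on one outcome only leaves its power at 81%. The gain shrinks to nothing in that case but never becomes a loss.

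**The case against.** A reader might infer something stronger: that hypothesis 1 joins the three outcomes with "and", so the trial has 54-67% power and not the 80% it states. The document does not support this. The Sample size section defines the test of hypothesis 1 as one test per outcome before it gives the 80%, and Statistical analyses repeats this with three separate models. The 80% is thus per-outcome power, and it is correct. No sentence promises 80% for all three together, and none says that all three must be significant. Dividing alpha by three makes sense only if each outcome can carry its own claim, and eligibility on PCBD and/or PTSD and/or depression fits that. If all three were required, no correction would be needed at all, so the shortfall under the joint reading cannot be the argument for Holm. This objection stands.

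It can also be said that 0.017 is only a sizing input, that Statistical analyses sets no threshold, and that a step-down rule may be left to an analysis plan not shown here. That is fair: sizing at 0.05/3 is compatible with Holm at analysis, and silence on it is not a fault. The point remains useful because 0.05/3 is the only multiplicity rule the article states.

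Finally, the size of the gain rests on assumptions. Zero correlation is pessimistic for syndromes that the Introduction describes as partly overlapping. The plan also enrols 55 and will include all participants in multilevel models. As an upper bound, 27 per arm with full information gives about 68-78% for all three under the fixed threshold at correlations 0 to 0.7. This softens the absolute figures but does not change the ordering of the procedures.

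**Conclusion.** The plan's correction is valid and its power statement is right per outcome. What holds is narrower: a fixed 0.05/3 for every test is stricter than 5% familywise control requires, and Holm is at least as powerful in every scenario. With f = 0.25 on all three outcomes, 46 completers and an assumed between-outcome correlation of 0 to 0.7, per-outcome power rises by about 6 to 9 points (81% to 87-90%). Over the same range, the chance of all three being significant rises by about 14 to 21 points (67% to 81% at correlation 0.7; 54% to 75% at 0). The gain is about 3 points per effective outcome if only two outcomes benefit, and nil if only one does. This is a worthwhile and nearly free improvement, not an error in the sample size.

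**What to change.** Prespecify Holm's procedure for the three hypothesis 1 tests: smallest p-value against 0.0167, next against 0.025, largest against 0.05, stopping at the first failure. Claim benefit only for the outcomes rejected. In the sample-size text, label the 80% as power per outcome at 0.017.

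State whether hypothesis 1 is judged per outcome or requires all three. If it requires all three, drop the correction and test each at 0.05; joint power is then about 76-83% under the assumptions above, and no claim may be made on one or two outcomes alone.

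The cost is a sentence or two. Models, data and enrolment do not change. The one small drawback is that simple simultaneous confidence intervals do not match Holm decisions exactly; 98.3% intervals can still be reported alongside, with a note that the decisions follow Holm.
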